### Data and statistical analysis

The primary analysis was done using the principle of intention-to-treat (ITT). ITT analysis includes participants with incomplete data, those who deviated from the study protocol and those who withdrew from the study. Missing data were handled through multiple imputation methods 
[43].

Socio-demographic, clinical characteristics and baseline information were presented to assess comparability between groups. Similar variables were also examined among the participants who withdrew from the study.

The primary endpoint of the study was the date when RTP was achieved or the end of week 16. Differences for categorical variables are tested with a chi-square test or Fischer’s exact test. As clinical outcome variables were repeatedly measured over time, a multivariate analysis of variance (MANOVA) for repeated measures was performed to explore an overall time, general group, and the time by group interaction effect.

Signs and symptoms changes were explored using linear regression analysis to determine the rate of change. In addition, levels of the various growth factors (IGF-1, bFGF and TGF) were determined. Statistical analyses were carried out using SPSS (Version 19). For all analyses, a value of *P* <.05 was considered significant.

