## Methods and design

### Study design

This study involved a randomised, assessor-blinded controlled trial of 16-week duration. Participants were screened before enrolment. Measurements (described below) were taken upon study enrolment. On day three following the PRP injection, the participants were reviewed for any adverse reaction. Subsequently, all the participants were reassessed once a week until the end of the study period. The protocol conformed to the CONSORT guidelines for nonpharmacological interventions 
[23].

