Participants in both groups were required to attend a weekly rehabilitation session with a physiotherapist until full recovery or the end of 16 weeks. At each visit, outcome measures were assessed, and rehabilitation programmes were conducted under a physiotherapist’s supervision. Each treatment session lasted for 45 – 60 minutes. Three-experienced physiotherapists (with at least five years of clinical experience) practicing at University Malaya Medical Centre and National Institute of Sports were trained to assess outcome measures and deliver rehabilitation programmes. The training involved a half-day course delivered by the principal researcher and a treatment manual. The treatment manual contained a brief summary of the study, assessment methods and hamstring rehabilitation based on the programme used by Sherry et al. 
[31]. In addition, the participants were expected to independently track their exercise compliance by recording the days they performed the prescribed rehabilitation programme on a logbook and to report any difficulties at each follow-up visit. The rehabilitation programme used in the study focused on progressive agility and trunk stabilization exercises (Table 
2). This programme was based on a set of exercises used in an earlier study 
[31]. Further, this programme was found to be more effective than a programme that only emphasized on hamstring stretching and strengthening in promoting RTP and preventing injury recurrence in athletes affected with an acute hamstring strain 
[31].

**Table 2 T2:** Rehabilitation programme

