### Primary outcome measures

In this study, primary outcome was the duration of RTP. Duration of RTP is defined as the duration (days) from the date of injury until the participants fulfil the criteria for RTP. The decision on determination of fitness for RTP is based on expert opinion 
[32]. As there were limited scientific studies done to examine the outcome of various RTP strategies 
[33], we decided to come up with our own criteria of RTP (Table 
3) based on recent clinical sports medicine recommendations 
[8,34-37].

**Table 3 T3:** Criteria for return-to-play (RTP)

**Sign**	**General Recommendation**
Pain	Pain-free (on direct palpation)
	Pain free on hamstring contraction (resisted isometric hamstring muscle contraction)
Range of motion	Symmetrical with unaffected site
Strength	Isokinetic strength within 5% [29,30] to 10% [8] of contralateral side

Direct hamstring palpation was conducted and pain elicited was recorded in the participants’ clinical research form (CRF). Pain provocation test was evaluated by isometric contraction of the hamstring muscles when palpation did not elicit any tenderness. This test was performed in prone lying with the knee flexed at approximately 15° 
[38]. Hamstring range of movement (ROM) was assessed using the active knee extension (AKE) test. The AKE test involves movement of the knee joint but not the hip, unlike the straight-leg raise (SLR) test which involves movements of both hip and knee joints. AKE test is an active test and is considered safe as the participants dictate the end point. This test has been recommended and often used to measure hamstring tightness. AKE test normal values of knee motion were reported to be within 20° on full extension of the knee 
[39].

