### Sample size

Sample size was determined using the following formula 
[42]:

(1)$$N=\frac{2\times {\left[z_{\left(1-\alpha /2\right)}+z_{\left(1-\beta \right)}\right]}^{2}\sigma^{2}}{{\left[\mu_{1}-\mu_{2}\right]}^{2}}$$

Where:

*N* = the sample size in each of the groups

$z_{\left(1-\alpha /2\right)}\;\text{of }.05$= 1.96 (percentage of the normal distribution for statistical significance level of .05)

$z_{\left(1-\beta \right)}\;\text{of }80\%$= .84 (percentage of the normal distribution for statistical power of 80%)

μ_1_ = population mean in treatment Group 1

μ_2_ = population mean in treatment Group 2

μ_1_ – μ_2_ = the mean difference

σ^2^ = population [standard deviation (SD)]

Total sample size after estimation of 30% attrition rate

= 11 + 3 = 14 participants in each intervention group giving a total of 28 participants altogether 
[7].

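### Participants who withdraw before return to play are right-censored, but the plan names only multiple imputation for missing data and no censoring or time-to-event method

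*Protocol article*

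**What the plan says.** The protocol article, under Primary outcome measures, gives the duration of RTP as "defined as the duration (days) from the date of injury until the participants fulfil the criteria for RTP". Under Data and statistical analysis it adds: "The primary endpoint of the study was the date when RTP was achieved or the end of week 16". Under Study design, "all the participants were reassessed once a week until the end of the study period", and the abstract says that readiness to return to play is judged at each follow-up visit.

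The analysis section describes the primary analysis as intention-to-treat: "ITT analysis includes participants with incomplete data, those who deviated from the study protocol and those who withdrew from the study". The next sentence reads "Missing data were handled through multiple imputation methods". The methods named after that are chi-square or Fisher tests, repeated-measures MANOVA and linear regression. No time-to-event method or censoring rule appears. The article does not say which variable is imputed, from what model, or within what limits. Under Sample size the number per group goes from 11 to 14 for an assumed 30% attrition.

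**The concern.** The point concerns participants who leave before week 16 without having met the criteria, not those who reach week 16 unrecovered. Because readiness is checked weekly, someone who leaves after a failed check is known to have an RTP time later than that check. That is a right-censored time, which carries more information than a missing value.

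Imputing the duration as an ordinary missing value has two consequences. First, a drawn RTP date can precede a visit at which the participant was seen not to qualify. Second, only participants who are still unrecovered can lose the outcome by withdrawing, so slow recoverers are over-represented among withdrawals even when the reason for leaving has nothing to do with prognosis. A model fitted to those with an observed RTP is then fitted to the faster recoverers, and it fills in values that are too short.

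Mean recovery time in each arm is at stake and, if withdrawal differs between arms, so is the treatment comparison in a trial of 28 participants.

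**Working it through.** The plan gives no figure for this analysis to reproduce, so the check asks what unbounded imputation would do.

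**Inputs from the protocol article**
- RTP time under the rehabilitation programme: mean 37.4, SD 27.6 days (Discussion).
- Attrition: 30% stated. The allowance actually made is 3 of 14 per group, 3/14 = 21.4% (Sample size).
- Visits weekly; follow-up 16 weeks = 112 days.
- Yardstick: the six-day effect quoted from a study of autologous conditioned serum (Background).

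**Assumptions (not in the document)**
- RTP times are lognormal.
- The withdrawal hazard is constant and unrelated to prognosis.
- Imputed durations are drawn from a normal distribution with the mean and SD of those with an observed RTP, with no other data used.

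**Lognormal parameters.** σ² = ln(1 + (27.6/37.4)²) = ln(1.5446) = 0.435, so σ = 0.659. μ = ln(37.4) − 0.435/2 = 3.404.

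**One participant, last failed check on day 28.**
- Chance that a draw from N(37.4, 27.6) falls before day 28: Φ((28 − 37.4)/27.6) = Φ(−0.34) = 0.37.
- Mean RTP time given T > 28: 37.4 × Φ((μ + σ² − ln 28)/σ) / Φ((μ − ln 28)/σ) = 37.4 × 0.779/0.544 = 53.6 days, against 37.4 if the failed check is ignored.

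**Whole arm, by simulation (2,000,000 draws).** The error in the arm mean is the withdrawal proportion times (mean of those observed − true mean of those withdrawn).
- At 30% withdrawal the observed mean is 31.8 days and the withdrawn participants' true mean is 50.4. Check: 0.7 × 31.8 + 0.3 × 50.4 = 37.4. Error: 0.3 × (31.8 − 50.4) = −5.6 days.
- At 10% the imputed-data mean is 35.6 against 37.4, an error of −1.8 days.
- In both cases 30–31% of imputed values fall on or before the last failed visit.

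**A different set-up.** Here enrolment is four days after injury, recovery is detected only at weekly visits, times are capped at week 16, and imputed values are drawn from the completers' own distribution. Days by withdrawal rate:

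| Distribution | Full-data mean | Imputed, 10% | Imputed, 21.4% | Imputed, 30% |
|---|---|---|---|---|
| Lognormal | 40.1 | 38.5 | 36.5 | 34.9 |
| Gamma | 40.6 | 38.7 | 36.4 | 34.5 |

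The shortfall is 1.6–1.9 days at 10% and 5.2–6.1 days at 30%, with 33–38% impossible values. A Kaplan–Meier restricted mean with withdrawals censored at the last visit returns 40.1 and 40.6 days at every rate.

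**Arm difference, first set-up.** Take a true six-day difference, with the SD in the PRP arm reduced in proportion to its mean.
- Equal withdrawal proportions of 10% to 30%: the difference becomes about 5.8 to 5.2 days.
- Equal withdrawal hazard, with 30% withdrawing in controls: 4.6 days.
- If the SD is instead 27.6 in both arms, a rerun gives 6.3 to 6.6 days with equal proportions, so the shift is still under one day.
- With 30% withdrawal in one arm and 10% in the other, the difference is off by 5.6 − 1.8 = 3.8 days.

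**The case against.** The strongest reply is that one sentence on multiple imputation does not fix a model. A reader might infer that the plan ignores the last visit and that its recovery times are biased short. The document does not say so, and details of the imputation may sit in a full protocol or analysis plan that is not shown. Pain, range of motion and strength are measured weekly. If those measures were imputed and RTP derived from them, no RTP date could precede the last attended visit. This stands: the figures above apply only if durations are imputed without the bound.

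The normal model is also crude, since about 8% of its draws are negative. That matters less, because draws from the completers' own distribution give a similar shortfall.

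A reader might further infer that the treatment effect itself is biased, or that a false PRP benefit is likely. The documents do not support that. The 3.8-day figure needs a 30% against 10% split that appears nowhere in them. Controls know that they had no injection, so unequal withdrawal is plausible, but it is not documented.

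Finally, one might infer from "At each visit, outcome measures were assessed, and rehabilitation programmes were conducted under a physiotherapist’s supervision" that a participant who stops rehabilitation loses the primary outcome. That sentence says only that the two share a visit. Study design has everyone reassessed weekly to the end of the study, and those who deviate from the protocol stay in the primary analysis. Telephone reports would be no substitute for missed visits, because the criteria require palpation, resisted contraction, range-of-motion and isokinetic testing.

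What the reply does not remove is the stated strategy: withdrawals are in the primary analysis, imputation is the only missing-data method named, and none of the named tests can use a censored time.

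**Conclusion.** The point holds in a conditional form. The outcome of an unrecovered withdrawal is right-censored at the last failed visit, and the plan names imputation for missing data without any method that uses this information. That is a choice of method for which a better one is available at little cost, so it is more than a detail left to another document.

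The size depends on an imputation model that is not stated. For unbounded imputation with withdrawal unrelated to prognosis, roughly three in ten imputed durations contradict an observed visit, and the arm mean is short by about 1.8 days at 10% withdrawal and 5.6 days at 30%. The latter is close to the six-day effect quoted in the Background, but it is an error in a single-arm mean. With similar withdrawal in both arms, the difference moves by less than a day and a half in the settings examined. Distortion of several days requires markedly unequal withdrawal, which is an assumption.

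**What to change.** In Data and statistical analysis, state that RTP is analysed as a time to event and that a participant who withdraws unrecovered is censored at the last visit at which the criteria were not met.

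If multiple imputation is kept, either impute the weekly pain, range-of-motion and strength measures and derive RTP from them, or draw only RTP times later than the last failed visit. In both cases add a sensitivity analysis that assumes later RTP for withdrawals than the main analysis does.

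The cost is slightly wider intervals and a little more analysis work. No participants, visits or procedures are added.

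### The repeated-measures MANOVA of the clinical outcomes names no adjustment for the enrolment value the trial already collects, which gives up precision in a 28-person trial

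*Protocol article*

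**What the plan says.** All places are in the protocol article.

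- **Study design:** "Measurements (described below) were taken upon study enrolment", and after the day-3 check for adverse reactions "all the participants were reassessed once a week until the end of the study period".
- **Injection technique** (the paragraphs on rehabilitation sessions): "At each visit, outcome measures were assessed". These weekly sessions run until full recovery or week 16.
- **PRP intervention group:** the injection follows randomisation, on day 1 of the study.
- **Data and statistical analysis:** the model is introduced with "As clinical outcome variables were repeatedly measured over time" and specified as "a multivariate analysis of variance (MANOVA) for repeated measures was performed to explore an overall time, general group, and the time by group interaction effect". The variables are not listed. The Primary and Secondary outcome measures sections suggest BPI-SF pain, active knee extension and isokinetic strength.
- **Same section, on baseline data:** "Socio-demographic, clinical characteristics and baseline information were presented to assess comparability between groups". No other use of baseline values is stated.
- **Same section, further analysis:** linear regression is planned for the rate of change of signs and symptoms, and P < .05 applies to every analysis.

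The article does not say whether the enrolment value is a level of the time factor, is left out of the model or is a covariate.

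**The concern.** A participant's own enrolment value usually predicts later values of the same outcome. With about 14 per arm, using it as a covariate removes between-person variance that otherwise stays in the error term of the group comparison. It also takes out the part of a chance baseline difference that carries forward. The listed effects (time, group, time by group) contain no such term.

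There is a second loss if enrolment is entered as a level of time. The group main effect then averages in a visit at which PRP cannot yet have acted, so the contrast is pulled toward zero.

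At stake is the chance of missing a real difference in the secondary clinical outcomes. Precision is scarce here: 28 participants, with 30% attrition expected.

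**Working it through.** **Inputs from the article:** 14 per group (28 in total); two-sided alpha 0.05, from the sample-size formula; weekly visits to week 16, so K = 16 post-enrolment visits. The day-3 review is described as an adverse-reaction check and is not counted.

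**Assumptions:** the article gives no effect size or correlation for these outcomes. I take SD 1 at every visit, a constant post-enrolment effect d = 0.8 SD, complete data, and a correlation that is either equal (0.5) or AR(1) per week (0.8, with 0.7 as a check). The article states no power figure for this analysis, so there is none to reproduce.

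**Formulas (equal correlation ρ)**

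- A. Enrolment as a level: effect d·K/(K+1), variance (1+Kρ)/(K+1).
- B. Post-enrolment mean, unadjusted: effect d, variance (1+(K−1)ρ)/K.
- C. Post-enrolment mean, adjusted for enrolment: effect d, variance of B minus ρ².

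Under AR(1) the same three contrasts are taken on the AR(1) matrix. In C the term subtracted is the squared covariance between the enrolment value and the post-enrolment mean.

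Non-centrality = effect × √(n/2) / √variance. Degrees of freedom are 2n−2 = 26 for A and B. For C they are 2n−3 = 25, with a factor √(1−1/26) = 0.981 for estimating the slope. Power is from the non-central t.

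**K = 16, ρ = 0.5, n = 14** (√(n/2) = √7 = 2.646)

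- Dilution in A: 16/17 = 0.94.
- A: variance 9/17 = 0.529; ncp = 0.8 × 0.941 × 2.646/0.728 = 2.74; power 75%.
- B: variance 8.5/16 = 0.531; ncp = 0.8 × 2.646/0.729 = 2.90; power 80%.
- C: variance 0.531 − 0.25 = 0.281; ncp = 0.8 × 2.646/0.530 × 0.981 = 3.91; power 96%.

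**Power under the different correlations, 16 visits**

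| Correlation | A: enrolment as a level | B: post-only, unadjusted | C: adjusted |
|---|---|---|---|
| Equal 0.5 | 75% | 80% | 96% |
| AR(1) 0.8 | 86% | 89% | 92% |
| AR(1) 0.7 | 95% | 96% | 97% |

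B − A is the cost of dilution alone: about 1 to 5 points. C − B is the gain from adjustment: 16 points at equal correlation 0.5, about 3 at AR(1) 0.8 and about 1 at AR(1) 0.7.

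**Sensitivity to fewer visits.** Sessions may stop at full recovery, so some participants may contribute fewer visits. With K = 4 the dilution is 4/5 = 0.80. Power is 56%, 73% and 90% at equal correlation 0.5, and 48%, 64% and 86% at AR(1) 0.8. Four visits is an illustration, not the stated schedule.

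**The case against.** **The article is silent, not wrong.** It lists effects and does not rule out a covariate, and a fuller protocol or SAP could contain one. This stands as far as it goes: the article cannot be read as saying that enrolment is treated as an outcome time point, or that it is ignored. The point survives because the article does specify a model by its effects, baseline adjustment is not among them, and the only stated use of baseline data is to present it.

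**A reader might infer that the group test is both diluted and unadjusted.** The text does not support that as a description of the plan. Dilution arises only if enrolment is a level, and then only in the group main effect. If enrolment is left out, there is no dilution, only lost precision.

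**Other planned analyses look at change.** With enrolment as a level, the time-by-group test compares changes over time and is not diluted in this way. The rate-of-change regression also addresses change. Both observations are correct, but neither replaces adjustment. Under the same assumptions and 16 visits, the multivariate interaction test (16 and 11 degrees of freedom) has power of about 17% at equal correlation 0.5 and 23% at AR(1) 0.8. A single-degree-of-freedom change from enrolment gives 80% at equal correlation 0.5, against 96% adjusted. The regression names no baseline adjustment either.

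**A reader might infer bias or a misleading result.** Randomisation keeps the unadjusted test valid, and its error rate already allows for chance imbalance. The loss is precision.

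**A large headline loss, such as 56% against 90%, is tempting.** It rests on four visits, which the article does not plan, and on enrolment being a level. About half of that gap (73% − 56% = 17 of 34 points) comes from the second assumption alone.

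**The analysis is exploratory.** It is worded as such and is not named as the analysis of duration to return-to-play. That limits the consequence, although the P < .05 threshold applies here too.

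**Conclusion.** The point holds as a free improvement in efficiency. The repeated-measures MANOVA is specified by time, group and time-by-group effects and names no baseline adjustment, while the outcomes are measured at enrolment. The unadjusted comparison is valid but less precise than it could be.

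Over the stated 16 weekly visits, adjustment against an unadjusted post-enrolment comparison is worth between about 1 point of power (AR(1) 0.7) and 16 points (equal correlation 0.5). If enrolment is also a level of time, a further 1 to 5 points are lost to dilution. Adjustment had the highest power of the three approaches in every scenario above. The size of the gain rests on the assumed correlation, the 0.8 SD constant effect and 14 complete participants per arm. A constant effect is itself doubtful while participants recover. That pain, range of motion and strength are the variables meant is a reading of the outcome sections, not a statement in the analysis section.

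**What to change.** For each repeated clinical outcome, take the enrolment value out of the response vector. Enter it as a covariate alongside group, visit and group by visit, and base the group contrast on post-randomisation visits only. A model that constrains the two arms to a common baseline mean serves the same purpose. The text should also name the outcomes and the visits that enter the model.

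The cost is a sentence in the analysis section and one error degree of freedom per model, already counted in the adjusted power figures. No new data or participants are needed. A missing enrolment value can be handled by the multiple imputation already planned.

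### A repeated-measures MANOVA suits the weekly outcomes badly in 28 participants: few error degrees of freedom if all 17 time points enter, and mostly incomplete series if assessment stops at recovery

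*Protocol article*

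**What the plan says.** Under Data and statistical analysis, the article says of the clinical outcomes measured repeatedly over time that "a multivariate analysis of variance (MANOVA) for repeated measures was performed to explore an overall time, general group" and time-by-group interaction effects. A separate sentence adds: "Signs and symptoms changes were explored using linear regression analysis to determine the rate of change". Missing data are to be handled by multiple imputation under intention-to-treat.

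The measurement schedule comes from other sections. Measurements are taken at enrolment (Study design), and follow-up is at day three and then weekly for 16 weeks (Abstract).

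The text differs on when the weekly assessments end. Study design says that "all the participants were reassessed once a week until the end of the study period", and one paragraph of Injection technique likewise has weekly reassessment to the end of the study. A later paragraph of the same section requires a "weekly rehabilitation session with a physiotherapist until full recovery or the end of 16 weeks", and says that outcome measures are assessed at each of these visits.

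The sample size section gives "11 + 3 = 14 participants in each intervention group giving a total of 28 participants altogether", the 3 per arm being the allowance for 30% attrition.

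**The concern.** The multivariate form of repeated-measures analysis estimates an unrestricted covariance matrix of the within-person contrasts. Each extra time point costs one error degree of freedom, and each participant must have a value at every time point, observed or imputed. Weekly measurement over 16 weeks in 28 people puts the number of contrasts close to the number of people.

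The time-by-group test is the part of this analysis that would show pain, range of motion or strength improving faster with PRP. If it has little power, a null result says almost nothing. If late values exist only for slow healers, the completed data lean on the imputation model rather than on measurement.

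**Working it through.** **Inputs**
- Participants: 28 (14 per arm), with 11 per arm (22) before the attrition allowance (Sample size).
- Time points: enrolment + 16 weekly visits = 17, so p = 16 within-person contrasts. Using all of them is an assumption. Counting day three would make 18.
- Groups: 2. Two-sided alpha 0.05 (Sample size, z = 1.96).
- Time to return-to-play under this rehabilitation programme: 37.4 ± 27.6 days (Discussion).

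The article states no degrees of freedom or power for the MANOVA, so there is no figure of its own to reproduce.

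**Step 1: degrees of freedom.** For time and time-by-group, numerator df = p and error df = N − 2 − p + 1.

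| Complete participants | Calculation | df |
|---|---|---|
| 28 | 28 − 2 − 16 + 1 | (16, 11) |
| 22 | 22 − 2 − 16 + 1 | (16, 5) |
| 20 (28 × 0.7 = 19.6) | 20 − 2 − 16 + 1 | (16, 3) |
| 18 | 18 − 2 − 16 + 1 | (16, 1) |
| 17 | 17 − 2 − 16 + 1 = 0 | not computable |

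The group main effect does not meet this limit: 28 − 2 = 26 df. With only 4 to 6 visits analysed and 28 complete, error df for the time effects are 24 to 22.

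**Step 2: power of the time-by-group test (illustrative).** Assume a group difference growing linearly to 1.19 SD at week 16, with AR(1) correlation 0.7 to 0.95 between weeks. The 1.19 is the standardised difference implied by 11 per arm in the article's sample size formula: √(2 × (1.96 + 0.84)² / 11) = √1.425 = 1.19. It belongs to the primary outcome and is borrowed only to fix a scale. The noncentrality is λ = (N/4) · δ′Σ⁻¹δ, where δ is the vector of 16 between-group differences in successive changes and Σ their covariance. Power is the upper tail of the noncentral F(16, N − 17).
- N = 28: λ = 5.68 to 8.86, power 12% to 18%.
- N = 22: λ = 4.46 to 6.96, power 8% to 10%.
- A one-df linear slope contrast over the same 16 weeks, under the same pattern, has 57% to 75% (N = 28) and 47% to 64% (N = 22).

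**Step 3: visits available if assessment stops at recovery.** Take recovery to mean meeting the return-to-play criteria, and time to recovery as lognormal. The log variance is ln(1 + (27.6/37.4)²) = 0.435, so the log SD is 0.659 and the log mean is ln 37.4 − 0.435/2 = 3.404.
- Day 56: (4.025 − 3.404)/0.659 = 0.94, so about 83% have recovered.
- Day 112: (4.718 − 3.404)/0.659 = 1.99, so about 98% have recovered.
- Expected participants with a series running to day 112: 28 × 0.023 = 0.65, fewer than one.

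A gamma distribution with the same mean and SD gives 80% and 98%, so the conclusion does not hang on the lognormal.

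**The case against.** Several points stand against a stronger reading.

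- *A reader might infer that the planned test has almost no error degrees of freedom.* With complete data 11 remain, and the group effect keeps 26. The article does not say that all 17 time points enter. With 4 to 6 chosen visits the MANOVA is workable, and visit selection is something a condensed article may leave to the full protocol. A univariate test with a sphericity correction would also avoid the limit, although the article names the multivariate method.
- *A reader might infer that assessments do end at recovery.* Only one paragraph says so, and its subject is rehabilitation sessions. Two other places run to the end of the study.
- *A reader might infer that MANOVA simply drops incomplete participants here.* Multiple imputation is planned, so complete visits are not formally required. What stands is that imputing most late visits in 28 people would be fragile.
- *A reader might infer that a mixed model removes bias from stopping at recovery.* It does not. It relies on the same missing-at-random assumption as the imputation.
- *A reader might infer that the rate-of-change regression has standard errors that are too small.* That holds only if weekly values are pooled across people. Regression slopes fitted per person are an equally natural reading, and would be sound.
- *A reader might take the slope contrast in the working as the obvious replacement.* Its advantage comes from assuming linear divergence. If the difference instead peaks at 1.19 SD near week 4 and then closes (an assumed bell shape), a linear slope over weeks 1–8 has only about 8–18% power against about 12–84% for the 17-point MANOVA. Since most participants should recover within eight weeks, such closing is plausible.

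The stakes are also limited. The MANOVA is described as exploratory, and the article claims no power for it.

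**Conclusion.** The concern holds in a conditional form. If all 17 time points enter, the time and time-by-group tests rest on 11 error df at best and 5 at the article's 22 participants, and are not computable below 18. Power is about 8–18% under the assumed linear divergence to 1.19 SD. Other shapes of difference give other figures, some much higher. If outcome assessment ends at recovery, virtually no participant would have a complete series, and the imputation would carry most of the late data. The contradiction on when assessment ends is in the text itself and needs settling whichever analysis is used.

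The documents do not show that the plan is unworkable, nor that its results would necessarily be biased. They show that the named method fits the described schedule poorly and that a better one is readily available. This is an improvement to exploratory analyses. It does not bear on duration to return-to-play, for which neither MANOVA nor a mixed model is suitable.

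**What to change.** 1. Replace the MANOVA with one linear mixed model per repeated outcome, using all observed visits, with baseline value, group, time and group-by-time. Use a parsimonious covariance: random intercept and slope (four variance parameters with the residual) or AR(1). An unstructured 17 × 17 matrix has 17 × 18 / 2 = 153 parameters and could not be estimated here.
2. Pre-state the group contrast in a form that allows for plateau and closing of the difference, such as the average group difference over a small fixed set of early visits, or a curved time trend. Do not rely on a linear slope alone.
3. If the rate-of-change regression is kept, base it on per-person slopes or take it from the same mixed model, not from pooled weekly values.
4. Reconcile Study design and the two paragraphs of Injection technique on when outcome assessment ends, and state one rule.

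The cost is analysis wording and a decision on the schedule text, with no added participants. The downsides are that the time trend and covariance must be given a form in advance, that no single contrast is best under every recovery pattern, and that late values still rest on a missing-at-random assumption if assessment stops at recovery.
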